## Abstract

**Background:**

The Canadian long-term care (LTC) workforce cares for increasingly complex residents. With greater care needs come greater demands. Despite this, LTC staffing and resources are largely unchanged and underresearched over the last decade. The Atlantic provinces are home to the oldest population in Canada, indicating a high need for LTC. The health and well-being of the LTC workforce are critical components of care quality, yet only in Western Canada are such data routinely and systematically collected. Translating Research in Elder Care is a 2-decade research program studying the LTC work environment and has found strong links between the working conditions of LTC staff and resident outcomes. We draw upon their success to generate the evidence needed to understand, support, and manage the LTC workforce in Canada’s four Atlantic provinces.

**Objective:**

This study aims (1) to assess the quality of work life among staff in LTC homes in Atlantic Canada; (2) to examine the effects of the work environment on the quality of work life; and (3) to build capacity for research in the LTC sector in Atlantic Canada among knowledge users, researchers, and trainees. The objective of this paper is to describe the approach needed to examine the quality of work life and health of care staff in LTC homes.

**Methods:**

Stratified random sampling will be used to recruit homes in Atlantic Canada. The sampling frame was designed to recruit 25% of the LTC homes in each of the 4 provinces with proportional representation by size; ownership model; and, if applicable, region or language. Key outcome variables include measures of mental health and well-being, quality of work life, intention to leave, workplace context, and missed or rushed care. Primary data will be obtained through structured interviews with care aides and web-based surveys from registered nurses, licensed practical nurses, managers, and allied health providers. Eligible participants were from an LTC home with at least 25 residents, 90% of whom were aged 65 years or older, and had worked in the home for at least 3 months. Multivariate analyses include regression analysis for explaining predictors of quality of work-life outcomes and multilevel modeling for more complex relationships of staff outcomes by provinces and LTC home characteristics.

**Results:**

Data collection and cleaning are complete as of October 2024 (N=2305). Care aides (n=1338), nurses (n=724), allied health providers (n=154), and managers (n=89) from 53 homes make up the sample. Data analysis is ongoing. Initially, individual reports will present descriptive data for each participating LTC home. Concurrent analysis is planned for publication in peer-reviewed journals.

**Conclusions:**

This peer-reviewed research protocol lays the foundation for a comprehensive analysis of the effects of the work environment on the quality of work life of LTC staff in Atlantic Canada.

**International Registered Report Identifier (IRRID):**

DERR1-10.2196/66338

## Introduction

### Background

This protocol is for a collaborative investigation that aims to address profound deficiencies in data to understand, support, and manage the long-term care (LTC) workforce in Canada’s 4 Atlantic provinces. In Canada, LTC homes are funded by provincial governments and provide a range of health and personal care services to predominantly older adults who require 24-hour nursing, personal, and support care [1]. Residents of LTC have higher levels of acuity and have more complex care needs than in the past decade as a result of increased life expectancy and delayed entry due to an increased emphasis on home care [2]. Approximately 81% of residents in Canadian LTC homes live with mild to severe cognitive impairment, 27.1% have seven or more chronic conditions, and 51.5% have extensive limitations in activities of daily living [3]. As the care needs of residents become greater, so do the demands placed on the LTC workforce. Despite this, LTC staffing and resources have remained largely unchanged and underresearched over the last decade [4,5].

The LTC workforce cares for residents with complex needs, but their work environments are strained by heavy workloads, inadequate resources, and critical staffing shortages [4,5]. The health and well-being of the LTC workforce are critical components of care quality [5], and yet only in the Western Canadian provinces of British Columbia, Alberta, and Manitoba are such data routinely and systematically collected [6]. In Atlantic Canada, no data are available on workforce characteristics or the work experiences of LTC care providers (ie, indicators of health, well-being, or burnout). LTC in Canada is provincially regulated, meaning policies, regulations, and practices differ among provinces; fundamental differences in how LTC is organized between Western provinces and Atlantic Canada influence how staff work and care for residents, including staffing models and ratios, and education and training requirements of staff. While many other Canadian provinces have continuously relied on internationally trained care workers to supplement the domestic workforce, this is a relatively new phenomenon in the Atlantic Canadian provinces of Nova Scotia, Prince Edward Island, Newfoundland and Labrador, and New Brunswick. Chamberlain et al [7] reported in 2018 that only 35% of care aides working in Alberta LTC homes spoke English as a first language in comparison to 95% of LTC care staff in a Nova Scotian 2021 pilot study [8]. Additionally, according to the 2021 census, between 96% to 99% of the population in Nova Scotia, Prince Edward Island, Newfoundland and Labrador spoke English as a first language, and as a bilingual province, nearly 70% of the New Brunswick population spoke English as a first language while the remaining 30% spoke French [9]. While recent efforts from governments in Atlantic Canada to bring internationally educated workers into LTC have been largely deemed successful from a recruitment perspective [10-12], little is known about how the changing composition of the workforce impacts the LTC environment. More specifically, it is unknown if, and to what degree, domestic and international staff feel supported as they adjust to a more diverse workplace. Further, the combined population of all 4 Atlantic provinces is fewer than 2.5 million [13] and far fewer staff are trained internationally. These differences limit the ability to generalize workforce data from the Western provinces to Atlantic Canada.

Given the relationship between work and care conditions [14,15], data on the LTC workforce are important as they allow policy makers to identify and address workforce issues that compromise resident care and the health and well-being of care staff. Understanding the work environment will assist in future workforce planning and the strategies designed to improve work conditions and ultimately care conditions.

### Translating Research in Elder Care

Translating Research in Elder Care (TREC) is a program of research spearheaded by [name] and a group of researchers from Alberta Canada who have been studying the LTC work environment in the Western Canadian provinces for nearly 2 decades [6]. TREC has analyzed the impact of the LTC work environment on staff quality of work life, mental health, and well-being outcomes in 7 waves of data collection [5,7,16-18]. These data enable in-depth longitudinal analysis that demonstrates the impacts of policy changes, interventions, and events such as COVID-19 [19-21]. The TREC research program also links the staff survey data within a clinical microsystem to resident outcomes using data from the Resident Assessment Instrument for LTC [22]. Evidence of strong links between the working conditions of LTC staff and resident outcomes is reported. For example, significant relationships were found between the use of best practices and care staff’s social capital and organizational slack (time and staffing) [23]. In examining the demographic profile of the LTC workforce, staff who provide the majority of direct resident care had little formalized training, were racially diverse, and had high rates of English as a second language [7]. More recently, TREC has designed and delivered interventions to enhance the work environment in LTC, such as Safer Care for Older Persons in (residential) Environments [21] and Improving Nursing Home care through Feedback on Performance [24], and a coherent breathing intervention to decrease stress, insomnia, and anxiety [25].

The TREC measurement system, including the care aide structured interview and the regulated staff web-based survey, were consistent with the instruments used in this study in Atlantic Canada. The minor exceptions were because of localized staff job titles and translation of survey instruments to enable staff in designated French LTC homes in New Brunswick to participate in their French language. The goal of our team is to build upon the work of TREC and to use their comprehensive data collection tools to build an Atlantic Research Collaboration (ARC) and to generate the evidence needed to understand, support, and manage the LTC workforce in Canada’s 4 Atlantic provinces. Ultimately, we will identify work environment areas that are amendable to intervention so that targeted interventions can be designed and delivered at the regional, provincial, institutional, and unit levels to enhance the quality of the LTC work environment.

### Study Purpose and Objectives

This ARC on LTC (ARC LTC) involved researchers and collaborators form 4 provinces to describe and examine the relationship between the health and quality of work life of LTC staff and their work environment (organizational context). The research aims are as follows.

To assess the quality of work life among staff in LTC homes in Nova Scotia, Prince Edward Island, Newfoundland and Labrador, and New Brunswick.To examine the effects of the work environment on quality of work life.To build capacity for research in the LTC sector in Atlantic Canada among knowledge users, early career researchers, and trainees.

## Methods

### Study Design

This is a cross-sectional, multilevel survey study with an integrated knowledge translation approach with knowledge users (ie, representatives from LTC homes, health authorities, provincial ministries, and key sector organizations) embedded throughout the project. We use the Checklist for Reporting Results of Internet E-Surveys (CHERRIES) reporting guidelines for web-based or internet surveys as a framework for our approach [26]. A detailed description using the CHERRIES checklist is present in Multimedia Appendix 1. Our methods are consistent with the established recruitment and data collection protocols used by TREC [23,27] and will enable comparison of data not only across the Atlantic Canadian provinces but also with the Western Canadian provinces.

### Study Context

The LTC sectors in Atlantic Canada are diverse with variations in names assigned to LTC homes, regulatory oversight, ownership models, and titles given to unregulated care staff (Table 1). The study’s design is sensitive to these differences with some modifications made to the sampling frame to reflect the uniqueness of individual provinces. In this protocol, we use the terms LTC home and care aide to describe the facility where care staff work or residents live, and the unregulated staff, respectively.

**Table 1 table1:** Characteristics of homes by province in 2023.

Characteristics	Nova Scotia	New Brunswick	Newfoundland and Labrador	Prince Edward Island	
Name of LTC^a^ homes	Nursing home	Nursing home	LTC homes	Manors or nursing homes	
Government responsible	Department of Seniors and LTC	Department of Social Development	Department of Health and Community Services	Department of Health	
Legislative framework	Homes for Special Care Act	Nursing Home Act	Health and Community Care Services Act	Community Care Facilities and Nursing Homes Act	
Ownership model	Public, private for-profit, and not-for-profit	Private corporations run by boards of directors	Public	Public, private for-profit, and not-for-profit	
Title for unregulated care staff or care Aides	Continuing care assistant	Resident aide	Personal care attendant	Resident care worker	
Regulated nursing staff	Registered nurses and licensed practical nurses	Registered nurses and licensed practical nurses	Registered nurses and licensed practical nurses		Registered nurses and licensed practical nurses
Allied health providers presence of these providers varies by province and LTC home	Recreation therapist, aide social worker, dietitian physiotherapist, aide occupational therapist, and aide	Recreation therapist, aide social worker, dietitian physiotherapist, aide occupational therapist, and aide	Recreation therapist, aide social worker, dietitian physiotherapist, aide occupational therapist, and aide		Recreation therapist, aide social worker, dietitian physiotherapist, aide occupational therapist, and aide

^a^LTC: long-term care.

### Theoretical Framing

The critical socioecological framework [28] is used to guide this research. This framework depicts how behaviors are influenced by characteristics of, and interactions between, the individual and immediate social network (microsystem), local environment or community (mesosystem), and the larger system (macrosystem). The ecological framework supports the bidirectionality of this influence (eg, the work environment may affect individual staff feelings of well-being and vice versa). The framework highlights the complexity of staff’s experiences and agency within the LTC environment and their ability to engage in change to enhance resident care. It acknowledges how the work environment is shaped and buffered by factors in the micro, macro, and meso levels. Embedding our research in the critical socioecological framework will enable us to examine the inter-relationships among individual experiences, the work environment, and the larger provincial and regional LTC policy context.

We will examine LTC at the macro, meso, and micro levels (see Multimedia Appendix 2 [29-39] for how the survey content is organized at the meso and micro levels). At the macro level, all 4 Atlantic provinces provide public funding to LTC. Although regulations, guidelines, and staffing ratios differ by province, individual homes vary in how they operationalize them internally. At the meso level, institutional practices, policies, and work culture, along with heavy workloads associated with complex LTC residents have a major impact on staff. About 80% of resident care in Canada is provided by unregulated care aides who have little, if any, formal education [7]. Despite their pivotal role in LTC, care aides may not receive the recognition they deserve, nor do they always feel like valued members of care teams [23]. Contextual factors in work environments such as leadership, culture, and social capital, influence individual staff at the micro level and account for greater job satisfaction, empowerment, and autonomy [40,41]. The critical socioecological framework can facilitate our understanding of the multilayered influencers on LTC staff’s quality of work life, and ultimately, resident care and quality of life in LTC homes in Atlantic Canada.

The dynamic nature of the LTC environment including things such as changes in the complexity of resident care needs and the increasing number of staff who speak English as a second language, could prompt changes in workplace policies and culture. Changes in both policies and culture can impact how staff work at the micro level as well as how organizations operate at the meso level. The nature of these bidirectional relationships affects how staff work, how they experience their work, and their perceived ability to support the changes needed in the work environment.

### Sampling

#### Facility Sampling and Eligibility

A stratified random sampling technique will be used to recruit homes from each of the 4 provinces. The sampling frame was designed to recruit 25% of the LTC homes in each province (Table 2) with proportional representation by size (large: >120 beds; medium: 70-119 beds; and small: 25-69 beds); ownership model (eg, public, not-for-profit, and private for-profit); and, if applicable, region or language. These strata have been previously associated with residents’ quality of care [42,43]. Oversampling will be done in Newfoundland and Labrador and Prince Edward Island to ensure a minimum of 8 homes in these provinces and a sufficient sample to enable cross-tabulation. Because Prince Edward Island only has 1 health region, and New Brunswick is a bilingual province with designated English and French homes, the region strata will not be used in Prince Edward Island, and linguistic designation will be used in New Brunswick.

To be eligible to participate, homes need to provide 24-hour, on-site housing and health care services for older adults by professional (nursing) staff, be stand-alone facilities (ie, not attached to an acute care hospital), and have a minimum of 25 LTC beds with at least 90% of the resident population aged 65 years or older. Homes will be ineligible if they are hybrid care homes integrated with an acute care facility or hospital, or share central services (eg, human resources and laundry) with an acute care facility or hospital.

**Table 2 table2:** Number of LTC^a^ homes included in the sample and strata by province (2023 estimates).

Characteristics	Nova Scotia	New Brunswick	Newfoundland and Labrador	Prince Edward Island	Total
Total number of LTC homes, n	92	73	43	19	227
Eligible homes, n (% of total)	81 (88%)	71 (97.3%)	27 (62.8%)	15 (78.9%)	194 (85.5%)
Sample (25% of eligible), n	20	18	8^b^	8^b^	54
Strata	Region ownership size	Language size	Region size	Ownership size	—^c^

^a^LTC: long-term care.

^b^Newfoundland and Labrador and Prince Edward Island were oversampled.

^c^Not applicable.

#### Staff Sample and Eligibility

Our sample will include senior administrators, managers, regulated nursing staff, unregulated care staff, and allied health providers (Table 3). All staff must have worked at the LTC home for 3 months or longer. In addition to the 3-month criteria, managers must work a minimum of 50% of the time at the LTC home, nurses must work a minimum of 6 shifts a month at the LTC home, care aides must be able to identify a unit they work on more than 50% of the time and work a minimum of 6 shifts a month on that unit, and allied health must provide at least one-third of their services that equals 6 days a month at the LTC home. Senior administrators who hold executive positions in LTC, such as chief executive and operation officers, will be required to provide the standardized facility (eg, physical design) and unit-level data (eg, staffing models).

**Table 3 table3:** Estimated number of care staff in LTC^a^—both regulated and unregulated by province.

Characteristics	Nova Scotia	New Brunswick	Newfoundland and Labrador	Prince Edward Island	Total by staff group
All registered nurses or licensed practical nurses in LTC, n	1611	2625	1278	299	5813
Sample pool from LTC homes (25%), n	322	656	320	150^b^	1448
Desired sample (60% of eligible staff), n	193	394	192	90	869
All care aides, n	3866	4875	962	710	10,413
Sample pool from LTC homes (25%), n	773	1219	241	355^b^	2588
Desired sample (60% of eligible staff), n	464	731	144	213	1553
Desired care staff (registered nurses, licensed practical nurses, or care aides) sample total, n	—^c^	—	—	—	2422

^a^LTC: long-term care.

^b^Prince Edward Island was oversampled (50%).

^c^Not applicable.

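### Table 3 takes Nova Scotia's staff pools at 20% under rows labelled 25%, so the total staff target of 2422 does not follow from the table's own rule

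*Protocol article*

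**What the plan says.** Under Facility Sampling and Eligibility, the plan for homes is "The sampling frame was designed to recruit 25% of the LTC homes in each province". The sample row of Table 2 is labelled "Sample (25% of eligible), n" and gives 20 homes in Nova Scotia, 18 in New Brunswick, 8 in Newfoundland and Labrador and 8 in Prince Edward Island. Its footnote names two departures: "Newfoundland and Labrador and Prince Edward Island were oversampled". Nothing marks Nova Scotia as different.

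Under Staff Sample and Eligibility, Table 3 starts from "All registered nurses or licensed practical nurses in LTC, n" and a matching row for care aides. It takes a pool from each, in rows labelled "Sample pool from LTC homes (25%), n", and then sets the desired sample at 60% of the pool. The only footnote on the pool rows puts Prince Edward Island at 50%. The desired samples total 869 nurses and 1553 care aides, together 2422.

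The Abstract reports what was obtained: "Care aides (n=1338), nurses (n=724), allied health providers (n=154), and managers (n=89) from 53 homes make up the sample".

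**The concern.** A reader who applies the labelled 25% can reproduce the pools for New Brunswick and Newfoundland and Labrador, and with the footnoted 50% those for Prince Edward Island. Nova Scotia cannot be reproduced. Both of its pools sit at 20%, so this is not a slip in one cell or a rounding effect: a different fraction was used and not disclosed. The Nova Scotia cells feed the 60% targets, both pool totals, both group targets and the overall 2422.

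At stake is the stated recruitment target. 2422 is the only total staff target in the article, and a reader judging recruitment will naturally set the achieved numbers against it. The affected province has the most homes (92 in total, 81 eligible), and comparison between provinces is part of the planned analysis.

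**Working it through.** **Inputs.** Staff counts, pools and targets are from Table 3, home counts from Table 2, and achieved numbers from the Abstract (1338 care aides + 724 nurses = 2062).

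**Step 1. Fraction actually used (pool / all staff).**

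| Province | Nurses | Care aides |
|---|---|---|
| Nova Scotia | 322/1611 = 20.0% | 773/3866 = 20.0% |
| New Brunswick | 656/2625 = 25.0% | 1219/4875 = 25.0% |
| Newfoundland and Labrador | 320/1278 = 25.0% | 241/962 = 25.1% |
| Prince Edward Island | 150/299 = 50.2% | 355/710 = 50.0% |

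The desired sample is 60% of the pool throughout.

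**Step 2. Reproduce 2422.** Target = sum over provinces of (all staff × pool fraction × 0.60). With Nova Scotia at 20%, New Brunswick and Newfoundland and Labrador at 25% and Prince Edward Island at 50%, the result is 868.5 + 1552.5 = 2420.9. That matches the printed figure up to rounding: the printed cells add to 869 + 1552 = 2421. The printed total therefore rests on 20% for Nova Scotia.

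**Step 3. Apply the labelled 25% to Nova Scotia.**
- Nurses: 0.25 × 1611 = 402.75, pool 403; × 0.60 = 241.65, target 242 (printed 322 and 193).
- Care aides: 0.25 × 3866 = 966.5, pool 967; × 0.60 = 579.9, target 580 (printed 773 and 464).
- Nova Scotia together: 242 + 580 = 822 against 193 + 464 = 657, a gain of 165 (25%). Unrounded, 0.05 × 0.60 × (1611 + 3866) = 164.3.
- Nurse totals: pool 403 + 656 + 320 + 150 = 1529; target 242 + 394 + 192 + 90 = 918.
- Care aide totals: pool 967 + 1219 + 241 + 355 = 2782; target 0.60 × 2782 = 1669.
- Overall target: 2422 + 164.3, about 2586 (+6.8%). Depending on where one rounds, it falls between 2585 and 2587.

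**Step 4. Does any home fraction in Table 2 explain 20%?**
- 20/81 eligible homes = 24.7%: pools 398 and 955.
- 20/92 of all homes = 21.7%: pools 350 and 840.
- 25% × 81/92 = 22.0%: pools 355 and 851.

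None gives 322 and 773. Across these readings and the labelled 25%, the printed Nova Scotia target of 657 is too low by about 57 (at 20/92: 0.60 × 5477 × 20/92 = 714) to 165 (at 25%).

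**Step 5. Sensitivity of the overall total.** Combined staff are 5477, 7500, 2240 and 1009 for Nova Scotia, New Brunswick, Newfoundland and Labrador and Prince Edward Island.
- Eligible-home fractions (20/81, 18/71, 8/27, 8/15): 0.60 × (1352.3 + 1901.4 + 663.7 + 538.1), about 2673.
- All-home fractions (20/92, 18/73, 8/43, 8/19): 0.60 × (1190.7 + 1849.3 + 416.7 + 424.8), about 2329. Nova Scotia still rises by 57, but New Brunswick falls by 15, Newfoundland and Labrador by 86 and Prince Edward Island by 48.

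**Step 6. Implied attainment of 2062.** 2062/2422 = 85.1%; 2062/2586 = 79.7%; 2062/2673 = 77.1%; 2062/2329 = 88.5%.

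**The case against.** A reader might infer that 2422 is simply 165 too low and that recruitment therefore looks better than it was. The documents do not settle that. The staff rows count all staff in long-term care, which may mean all homes, whereas Table 2's 25% refers to eligible homes. If all-home fractions were meant in every province, the total would be about 2329 and 2422 would be too high. The direction of the overall error is therefore open. What stands is that Nova Scotia's cells are too low on every fraction the article documents.

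It is also tempting to call 2422 the only sample-size figure. It is not: the article plans 54 homes and gives separate targets of 869 and 1553. Homes are the randomly selected unit, and 53 took part.

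Nor does the article state an attainment percentage, so there is no misleading claim of that kind to retract. Table 3 is headed as an estimate, and the eligible staff in each home were to be verified at orientation. For that reason 2062 divided by the Table 3 pool should not be read as a response rate. The article ties no power or precision calculation to 2422. All of this limits the consequence. None of it explains 20% under a 25% label.

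**Conclusion.** The inconsistency is real and can be checked from Tables 2 and 3 alone. Nova Scotia's pools are 20.0% in both staff groups, the rows say 25%, no footnote covers the difference, and no Table 2 fraction produces it. Under the labelled rule, Nova Scotia's target is short by about 165 and the total by 6.8%. That size assumes the 25% label is what was intended. If 20% was intended, the label is wrong for Nova Scotia and a footnote is missing, so the table needs correcting either way.

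A related mismatch belongs to the same correction. Newfoundland and Labrador is described as oversampled in Table 2 (8/27 = 29.6% of eligible homes, but 8/43 = 18.6% of all homes), while Table 3 keeps it at 25% without comment. The effect is confined to the stated recruitment target and whatever attainment a reader infers from it. No estimate, power statement or planned analysis changes.

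**What to change.** Apply the labelled 25% to Nova Scotia: pool 403 and target 242 for nurses, 967 and 580 for care aides. Restate the totals as about 1529 and 918 for nurses, about 2782 and 1669 for care aides, and about 2586 overall. If 20% was intended, say so in a footnote and explain why it differs from 20 of 81 homes in Table 2.

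In the same correction, state whether the all-staff counts cover all homes or only eligible homes, and either footnote Newfoundland and Labrador's 25% or replace it with the fraction that follows from Table 2. If attainment is later reported, set the 2062 nurses and care aides, without managers and allied health providers, against the restated target.

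The cost is a table correction, one or two footnotes and restated totals. Data collection is complete, so nothing further is collected and no analysis is rerun.
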